## Abstract

**Background:**

Myocardial infarction remains as a major cause of mortality worldwide and a high rate of survivors develop heart failure as a sequel, resulting in a high morbidity and elevated expenditures for health system resources. We have designed a multicenter trial to test for the efficacy of autologous bone marrow (ABM) mononuclear cell (MC) transplantation in this subgroup of patients. The main hypothesis to be tested is that treated patients will have a significantly higher ejection fraction (EF) improvement after 6 months than controls.

**Methods:**

A sample of 300 patients admitted with ST elevation acute myocardial infarction (STEMI) and left ventricle (LV) systolic dysfunction, and submitted to successful mechanical or chemical recanalization of the infarct-related coronary artery will be selected for inclusion and randomized to either treated or control group in a double blind manner. The former group will receive 100 × 10^6 ^MC suspended in saline with 5% autologous serum in the culprit vessel, while the latter will receive placebo (saline with 5% autologous serum).

**Implications:**

Many phase I/II clinical trials using cell therapy for STEMI have been reported, demonstrating that cell transplantation is safe and may lead to better preserved LV function. Patients with high risk to develop systolic dysfunction have the potential to benefit more. Larger randomized, double blind and controlled trials to test for the efficacy of cell therapies in patients with high risk for developing heart failure are required.

**Trial Register:**

This trial is registered at the NIH registry under the number NCT00350766.

## Background

Acute myocardial infarction (AMI) is a major cause of mortality worldwide. Many survivors of AMI develop heart failure, associated with a high morbidity that worsens their quality of life and generates elevated expenditures for health system resources.[1].

Heart Failure (HF), which has ischemic cardiomyopathy as its most frequent cause, is an epidemic disease of this century. It affects from 2 to 4 million people in the United States (US), and 15 million people around the world.[2] HF in Brazil generates more than 260.000 hospitalizations per year, representing the fourth major cause of hospitalization (2.60% of all hospitalizations in 2007) with an in hospital mortality of 8.1%.[3].

Different medical therapies are efficient for patients who develop systolic dysfunction after AMI, as ACE inhibitors and beta blockers, which aim to improve the infarct repairing response. Recently, cell therapy has appeared as a new perspective. Growing evidence suggests benefits of cell therapies in repair or regeneration the myocardium, and several types of cells have been used. However, cellular and molecular mechanisms responsible for the ventricular function improvements, which have been reported in most of the studies, are still poorly understood. Among other questions, the best pathway to introduce stem cells into the heart has been investigated for the treatment of ischemic cardiomyopathy.

To our knowledge, five other clinical trials of autologous bone marrow (ABM) mononuclear cell (MC) transplantation through intracoronary injection after AMI were published, with more than 300 patients tested and followed for at least 1 year. [4-10] Importantly, no adverse effects associated to the injection procedure were reported.

Even though these are still preliminary data, the results have led us to investigate cell therapy as an alternative treatment of ischemic cardiomyopathy following acute myocardial infarction.

### Hypothesis

The main hypothesis of this trial is that patients submitted to autologous bone marrow stem cell transplantation will present, on average, at least 5% higher EF in comparison with the placebo group after 6 months follow up.

## Methods

This research protocol integrates the Multicenter Randomized Trial of Cell Therapy in Cardiopathies (MiHeart Study) which has been already published.[11] MiHeart Study is divided in four main branches: Dilated Cardiomyopathy; Chagas Disease; Chronic Ischemic Cardiomyopathy and Acute Myocardial Infarction. Here we detail the protocol of the Acute Ischemic Cardiomyopathy branch which was approved by the Institutional Review Board/Ethics Committee at each center including the Anchor Center (PROCEP, Rio de Janeiro) and by the Brazilian National Ethics Council for Human Research (CONEP, Brasilia) in accordance with the principles outlined in the Declaration of Helsinki and National Health Council Resolution n° 196/96.

### Study design

Multicenter, double blind, randomized and placebo controlled trial.

### Population and enrollment

Three hundred patients with ST elevation AMI (STEMI) submitted to successful mechanical (TIMI flow grade 3) or chemical recanalization of the culprit coronary artery up to 24 hours after symptoms onset, and presenting EF ≤ 50% will be selected for inclusion.

Patients will be eligible if presenting all the following characteristics: [1] STEMI; [2] age between 30 and 80 years; [3] EF ≤ 50% (Simpson) and [4] regional dysfunction in the infarct-related area, measured before cells injection. Among patients submitted to fibrinolytic therapy, the angioplasty of the related artery should be done up to 72 hours after fibrinolysis. All patients will be treated with Liberte™ stents, generously donated by Boston Scientific Corp., Natick, Massachusetts.

Patients will be excluded if presenting any of the following: obstruction >50% on Left Main Coronary Artery or multivessel coronary disease, indicating the need for CABG (Coronary Arterial Bypass Grafting); coronary anatomy presenting no need for angioplasty with stent implant; final diastolic pressure of left ventricle (LV) higher than 30 mm Hg during initial ventriculography; cardiac arrest or Killip IV at admission with the need of ventilatory support; cardiogenic shock persisting up to the third day after symptoms onset; mechanical complications of AMI; significant valve disease; chronic use of immunosuppressant agents; >2,0 mg/dl creatinine or previous dialysis treatment; sepsis; sustained ventricular tachycardia after 48 hours post-AMI; illicit drugs abuse or alcohol abuse (based on DSM IV); myocarditis; active liver disease; severe COPD (Chronic Obstrutive Pulmonary Disease); hematological disease, neoplasm, bone disease or haemostatic disturbances; inflammatory disease or chronicle infectious disease; presence of definitive implantation of a cardiac pacemaker or cardiac defibrillator or any co-morbidity, with survival impact in 2 years.

Patients will be included only after signing Informed Consent form, written in accessible language and with information about all relevant aspects regarding the research protocol.

### Randomization

A computer-random number generator will perform randomization procedure in the day of injection as previously published in Trials.[11] Briefly, software was created in R version 1.9.0 to specifically generate the randomization sequence for the study. It is known that a simple randomization is sufficient and efficient to render the study groups homogeneous for known and unknown factors in large scale clinical trials. To insure homogeneity in the two arms of the study we adopted block randomization. We will use randomization by variable size block (blocks of 2, 4 or 6 patients). Patients will be randomized after bone marrow aspiration and only the hematologist responsible for cell separation will have the login and password to randomize the patient online. According to the assigned group, darkened syringes containing the mononuclear cell fraction or saline with 5% autologous serum will be then prepared and sent for injection.

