#### ✓ Baseline exams (before bone marrow aspiration) and follow up

The chronogram of the study is shown in table 2. Briefly, patients will be submitted to a clinical evaluation at hospital admission and clinical data regarding blood pressure, heart rate and Killip and Kimball classification will be stored. Patients will be standardly treated with chemical or mechanical reperfusion according to the local center availability. A coronary angiography and an invasive ventriculography will be performed in all patients before angioplasty in order to evaluate inclusion/exclusion criteria. Patients submitted to fibrinolysis must have the angioplasty of the infarct-related coronary artery performed up to 48 hours after reperfusion. Laboratorial dosage will be also performed as shown in table 2.

**Table 2 T2:** Chronogram of the study

Informed Consent	□											
Randomization				□								

**Exams/Visits**					**After Injection**							
										
	Baseline	pos-reperfusion	3^rd^–5^th ^day of reperfusion	5^th ^to 7^th ^day	Up to 1 h	12 h	24 h	6^th ^to 9^th ^day	1 month	3 months	6 months	1 year

Medical visit	□		□						□	□	□	□
ALT, AST, AP, PT, aPTT and INR			□									
Total Cholesterol, LDL-cholesterol, HDL-cholesterol and Triglycerides	□											
Full blood panel, Glucose, Urea, Creatinine, Na+, K+, CRP			□				□		□		□	
CK-MB mass, Troponin I	□		□	□		□	□					
Electrocardiogram	□	□	□		□	□	□		□	□	□	□
Echocardiogram			□						□	□	□	□
Cardiac MRI								□			□	
Coronary angiography	□										□	
Cells transplant				□								
Cells sample storage				□								
SF-36, Minnesota and Seattle QOL			□						□		□	□
QALY Evaluation									□		□	□

ALT and AST: alanine and aspartate aminotransferases, respectively; AP: alkaline phosphatase; INR: international normatized ratio; PT: prothrombin time; aPTT: activated partial thromboplastin time; CRP: C-reactive protein; MRI: magnetic resonance image; QOL: quality of life questionnaires; QALY: quality adjusted life year.

Three to five days after reperfusion therapy (mechanical or chemical), patients will be submitted to another clinical evaluation, including an EKG, an echocardiogram and laboratory tests, from which results will be used as baseline data for the research protocol, before injection procedure. A new CK-MB mass and troponin dosage will be performed in the morning preceding the injection procedure and timely in the 24 hours following the injection.

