The baseline cardiac magnetic resonance imaging (MRI) will be performed between day 6 and 9 after the AMI-related coronary artery recanalization. This exam may be performed either in the hospital or at a reference hospital. All imaging exams will be evaluated off line by the core lab specified in the appendix [see Addition file 1].

Hospital discharge is predicted 24 hours after cell transplantation unless otherwise indicated, making a total length of stay of approximately 7 days. Patients will be provided with clopidogrel, aspirin and pravastatin during the entire study and treated at the discretion of the attending physician.

Patients will be followed for 1 year after the procedure according to the chronogram of the study shown in table 2. All imaging exams will be stored and sent to the core lab for independent analysis as specified in the appendix [see Addition file 1].

Cardiac MRI will be done by the local centers with commercially available software, electrocardiographic triggering, and cardiac-phased array coil. LV function will be assessed by the use of steady-state free-precession gradient-echo sequence (SSFP). Eight to twelve short axis slices will be acquired during a 10–15 seconds breath-holding allowing for coverage of the entire LV. Additionally, 3 long-axis views will also be acquired: 2-chamber and 4-chamber views and left ventricle out flow tract. Regional LV function will be assessed by measuring systolic wall thickening in the infarct region, the adjacent border zone and remote myocardium and semi-quantitatively assessed, using a 17-segment model[14].

Transmural extent of late hyper-enhancement within each segment will be graded according to the following classification: 0–25%, 26–50%, 51–75%, and more than 75% hyper-enhancement. Segmental functional recovery is defined as an increase from hypokinetic to normokinetic, from akinetic to hypokinetic or normokinetic, or from dyskinetic to akinetic, hypokinetic, or normokinetic. Infarct size will be measured by planimetry.

Microvascular obstruction will be defined on late enhanced images taken early (within 2–5 min) after injection of 0.20 mmol/kg of gadopentetate dimeglumine (Gd-DTPA), in the LV short and long axis at the same locations used for cine-MRI–as a dark, subendocardial zone within the infarct area.

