### End points and statiscal analysis

The primary endpoint of this trial is the global left ventricular EF change from baseline to 6 month follow-up.

The following secondary endpoints will be evaluated for up to 1 year of follow up: major cardiovascular events (all-cause mortality, acute myocardial infarction, stroke and hospital admission due to cardiovascular cause); reintervention of the AMI-related artery and of non-related arteries; by MRI regional wall motion, wall thickening, and volume of late contrast enhancement; quality of life assessment using the Short-Form 36, Minnesota Living with Heart Failure and Seattle Angina questionnaires; cost-effectiveness and cost-utility evaluation of ABMMC implant versus conventional treatment.

All outcomes will be analyzed by intention to treat.

Primary outcome will be analyzed by comparing EF, measured by MRI, between groups, using student t test or Mann-Whitney according to the sample distribution. Two evaluations are programmed:

1. Interim analysis, which will use data related to patients 1 to 150;

2. Final analysis, which will use data related to all 300 patients.

Secondary outcomes will only be evaluated after the main final analyses. Mortality and functional class improvement will be analyzed by non-corrected chi-square test. Continuous variables with normal distribution will be analyzed by t student test and ANOVA for repeated measures. Continuous variables with asymmetric distribution and quality of life scores will be analyzed by Mann-Whitney test and ANOVA for repeated measures.

The frequency of serious adverse events (which brings eminent risk of death or permanent disability) will be analyzed by chi-square or Fisher's test.

The trial can be interrupted after interim analysis; using the O'Brien and Fleming rule for two sequential tests and the 5%, in which the null hypothesis is rejected if:

• p ≤ 0,0050 in the first analysis;

• p ≤ 0.04806 in the final analysis.

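### The primary test leaves centre and reperfusion-route variation in its error, and blocking is credited with a balance of the arms that it does not itself give

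*Protocol article*

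**What the plan says.** The design is given as "Multicenter, double blind, randomized and placebo controlled trial" (Study design). The Randomization section first states that "It is known that a simple randomization is sufficient and efficient to render the study groups homogeneous for known and unknown factors" in large trials. It continues "To insure homogeneity in the two arms of the study we adopted block randomization" and gives the block sizes as 2, 4 or 6. It names no stratification factor and does not say that there is none. The paragraph is a short summary that refers to an earlier publication for the full method.

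The section on baseline exams and follow-up says "Patients will be standardly treated with chemical or mechanical reperfusion according to the local center availability". On imaging it says "Cardiac MRI will be done by the local centers with commercially available software", with reading by a core laboratory. The section on end points and statistical analysis defines the primary endpoint as EF change from baseline to 6 months. The groups are to be compared "using student t test or Mann-Whitney according to the sample distribution". No test named there, primary or secondary, carries a term for centre or reperfusion route.

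**The concern.** Two statements need attention.

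The first is the reason given for blocking. A permuted block forces equal arm counts at the end of each block and does nothing else. It balances a patient factor only if blocks run separately within levels of that factor. As written, the sentence credits blocking with something it does not do.

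The second is the analysis. The protocol's own text makes centre a plausible source of variation in outcome, through reperfusion route and image acquisition. An unadjusted test counts that variation as noise. With one central list, the result is lost precision. With per-centre lists, the design removes centre differences from the treatment contrast but the test still charges for them, so its standard error is too large and the test is conservative. In either case a model with centre uses the data better, provided that centres differ in EF change.

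**Working it through.** **The plan's own figure.** The Sample size section gives 143 per arm for a 5-point difference with SD 5, 95% confidence and 80% power. The usual formula gives n = 2(1.96 + 0.84)² × 5²/5² ≈ 16 per arm, so 143 is not reproduced. That is a separate matter, but it affects which effect to use here. At 143 per arm and the databank SD of 7.9, the difference detectable with 80% power is 7.9 × 2.80 × √(2/143) = 2.62 points, or 2.62/7.9 = 0.33 SD. This effect puts the unadjusted test at its planned 80%. Power results depend only on this ratio and the centre share, not on the SD itself.

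**Assumptions.** The documents give neither the number of centres, nor the share ρ of variance between centres, nor the proportion given fibrinolysis. I take 10 or 25 centres, ρ of 0 to 20%, and 286 evaluable patients (2 × 143). Tests are at two-sided 0.05, which ignores the small adjustment to 0.04806 at the final analysis.

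**Closed form, centre fully balanced and fully removed.**
- Ratio of unadjusted to adjusted standard error: 1/√(1−ρ) = 1.026, 1.054 and 1.118 for ρ = 5, 10 and 20%.
- True error of the unadjusted test with per-centre lists: 2(1 − Φ(1.96/√(1−ρ))) = 4.4, 3.9 and 2.8%.
- Power with adjustment: Φ(2.80/√(1−ρ) − 1.96) = 82.0, 84.0 and 87.9%, against 80%.

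**Simulation with blocks of 2, 4 or 6.** Adjustment here uses fixed centre effects (3000 null and 2000 alternative runs per cell).

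| Centres | ρ | Per-centre lists: true error, unadjusted | Per-centre lists: power, unadjusted to adjusted | Single list: power, unadjusted to adjusted |
|---|---|---|---|---|
| 10 | 5% | 4.2% | 82.5 to 83.5 | 79.9 to 80.2 |
| 10 | 10% | 4.5% | 81.3 to 83.3 | 80.7 to 83.0 |
| 10 | 20% | 3.2% | 83.1 to 88.3 | 79.9 to 86.0 |
| 25 | 5% | 4.7% | 81.7 to 82.2 | 79.8 to 77.5 |
| 25 | 10% | 3.6% | 80.4 to 82.8 | 78.8 to 79.5 |
| 25 | 20% | 3.1% | 82.5 to 88.2 | 80.6 to 84.7 |

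The Monte Carlo standard error of the 5% level is √(0.05 × 0.95/3000) = 0.4 points, so the values at ρ = 5% are hardly distinguishable from nominal. The one loss of power is with 25 centres and ρ = 5% on a single list, where many fixed effects buy little.

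**The proposed model.** With a random centre intercept in place of fixed effects (10 or 25 centres, ρ from 0 to 20%, 286 patients), type I error stays near 5%. Power is about unchanged at ρ = 0 and up to about 7 points higher at ρ = 20%, under either kind of list.

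**Validity on a single list.** With 300 patients and ρ of 10 to 30%, the unadjusted t test has a type I error of 4.8 to 5.7%, nominal within simulation noise.

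**Reperfusion route.** If 30% of patients receive fibrinolysis (an assumption), the arm difference in that share has standard error √(0.3 × 0.7 × 2/150) = 5.3 points. Its absolute value averages 0.80 × 5.3 = 4 points, with a 95th percentile of 1.96 × 5.3 = 10 points. The documents do not say how far route affects EF change, so no power figure is attached to it.

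**The case against.** The strongest reply has four parts.

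- **The summary is not the full method.** The section points to an earlier publication, so silence on strata cannot be read as absence of strata. This stands. A reader might infer that the trial is unstratified; the documents do not support that.
- **Nothing is invalid.** Randomization balances centre and route in expectation with or without strata, and the unadjusted test is either at its nominal level or conservative. This also stands. It would be wrong to conclude that the arms will not be comparable, or that the trial's error rate is inflated.
- **The centre share is assumed and may be small.** The endpoint is a change, so a constant scanner or case-mix offset largely cancels, and core-laboratory reading removes some variation. Fibrinolysis patients also undergo angioplasty and all patients receive stents, which narrows the route contrast. Site differences in cell preparation act in the treated arm only, and a centre intercept would not remove them. On the plan's stated 5 points with SD 5 or 7.9, power at 143 per arm exceeds 99.9% whatever is done. All of this limits the size. It does not make the unadjusted test preferable: the interval would still be wider by the ratios above if centres differ, and the stated inputs do not yield the stated sample size, so they are no safe cushion.
- **Adjustment may sit in an analysis plan that is not shown.** This stands only in part. The article does not leave the primary test open; it names one, and a plan that adjusted for centre would depart from it.

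**Conclusion.** The concern holds as a matter of precision and wording. Blocking is credited with homogeneity when it balances arm numbers only, and the named primary test leaves any centre or route variation in EF change in its error. The gain from a random centre intercept is about 0 to 7 points of power for an assumed centre share of 0 to 20%. If the lists are per centre, the unadjusted test runs at about 3 to 5% instead of 5% for an assumed share of 5 to 20%. These figures rest on assumed centre numbers and variance shares, and on an effect of 0.33 SD.

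A reader might go further and call for per-centre blocks from now on. The documents do not support that as a clear improvement. The lists may already be per centre, and recruitment began in August 2006, so it could mean a change of scheme in mid-trial. The staff who prepare the syringes know past assignments, and blocks as small as 2 within a centre make the next one easier to guess.

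**What to change.** In the section on end points and statistical analysis, make the primary comparison a linear model of EF change with treatment, a random centre intercept and reperfusion route (chemical or mechanical). Both covariates are known before randomization, so adjusting for them is safe. Keep the unadjusted test as a sensitivity analysis.

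In the Randomization section, reword the sentence to say that blocks balance arm numbers, and state whether the lists are per centre. Leave the allocation scheme as it is during recruitment.

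The cost is a slightly longer model specification. No extra patients or measurements are needed. If centre variance is near zero, there is little gain and, with a random intercept, about no loss of power.

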### Cell transplantation Phase

#### ✓ Bone marrow aspiration procedure

About 100 ml of bone marrow aspirate will be harvested from iliac crest between the 5^th ^and 7^th ^day after myocardial reperfusion therapy under local anesthesia and sedation at an intensive care unit or surgical center. The aspiration procedure will be done by using a 1.8 mm Jamshidi needle.

ABMMC will be isolated by density gradient centrifugation on Ficoll- Paque™ plus^® ^(Amersham Biosciences) and manipulated under aseptic conditions. 100 × 10^6 ^cells will be resuspended in 10 ml saline solution with 5% autologous serum and filtered through 100 μm nylon mesh to remove cell aggregates for injection. A fraction of the cell suspension will be used for cell counting and viability testing with trypan blue exclusion. Cell viability must be above 90% to be injected. Post-hoc characterization of leukocyte differentiation markers by flow cytometry (table 1) and functional assays will be done on another fraction of cells. This last evaluation concerns clonogenic capacity of marrow progenitors by colony-forming assays (granulocyte-macrophage colony-forming units – CFU-GM, vascular-endothelial cell colony-forming unit – CFU-VE, and fibroblast colony-forming assay – CFU-F), as previously described.[12,13]

**Table 1 T1:** Post-hoc characterization of leukocyte differentiation markers

**Phenotype**	**Intended designation**
**1**. CD45^lo^CD34^+^	ISHAGE protocol
**2**. Lin^-^CD45^lo^CD34^+^	Hematopoietic progenitors
**3**. Lin^-^CD45^lo^CD34^+^CD133^+^CD117^+^	Hematopoietic stem cells*
**4**. Lin^-^CD45^-^CD133^+^CD31^+^CD144^+^KDR^+^	Endothelial precursor*
**5**. Lin^-^CD45^-^CD133^-^CD31^+^CD144^+^KDR^+^	Endothelial cell*
**6**. CD45^+^CD10^+^CD33^+^HLA-DR^-^CD45RA^-^	Myeloid precursor*
**7**. CD45^+^CD10^+^CD33^-^HLA-DR^+^CD45RA^+^	Lymphoid precursor*
**8**. CD45^-^CD133^+^CD146^+^CD144^+^CD166^+^	Mesenchymal progenitor*
**9**. CD45^-^CD133^-^CD146^+^CD73^+^CD166^+^	Mesenchymal cell*
**10**. CD45^+^CD10^+^CD34^+^CD19^-^CD38^-^TdT^+^IgM^-^	pre-pro-B intermediary
10.1. CD45^+^CD10^+^CD34^+^CD19^+^CD38^-^TdT^+^IgM^-^	pro-B/pre-B I intermediary
10.2. CD45^+^CD10^+^CD34^-^CD19^+^CD38^-^TdT^-^IgM^-^	Pre-B II intermediary
10.3. CD45^+^CD10^-^CD34^-^CD19^+^CD38^+^TdT^-^IgM^+^CD24^hi^	Immature B LΦ
10.4. CD45^+^CD10^-^CD34^-^CD19^+^CD38^+^TdT^-^IgM^+^	Naïve B LΦ
10.5. CD45^+^CD10^-^CD34^-^CD19^+^CD38^+^TdT^-^IgM^+^CD24^lo^CD69^+^	Mature B LΦ
**11**. CD45^+^CD34^+^CD38^-^CD1a^-^CD3^-^CD4^-^CD8^-^	LΦ-T DN1
11.1. CD45^+^CD34^+^CD38^+^CD1a^-^CD3^-^CD4^-^CD8^-^	LΦ-T DN2
11.2. CD45^+^CD34^+^CD38^+^CD1a^+^CD3^-^CD4^-^CD8^-^	LΦ-T DN3
11.3. CD45^+^CD34^+^CD38^+^CD1a^+^CD3^lo^CD4^+^CD8^-^	LΦ-T DN4-ISP
11.4. CD45^+^CD34^+^CD38^+^CD3^-^CD4^+^CD8^+^	LΦ-T DP
11.5. CD45^+^CD34^+^CD38^+^CD3^+^CD4^+^CD8^+^	LΦ-T DP-CD3
**12**. CD45^+^CD34^+^CD3^+^CD4^+^CD8^-^	LΦ-T CD4
**13**. CD45^+^CD34^+^CD3^+^CD4^-^CD8^+^	LΦ-T CD8
**14**. CD45^+^CD122^+^CD56^+^CD3^-^	NK cells
**15**. CD45^+^CD66acde^+^	Neutrophils/Basophils
**16**. CD45^+^CD41a^+^	Megakaryocytes
**17**. CD45^+^CD66acde^-^CD41a^-^CD14^+^CD16^+^	Monocytes/Macrophages

*The intended designation to some phenotypes will be more deeply explored with additional markers like CD117, CD31, CD105, CD106, CD166 and others of interest. Besides, cell subpopulations also will be sorted to perform supplementary function assays.

An out of hospital independent team at each site, composed by 2 biologists trained by the anchor center, will be the responsible for cell separation and preparation of the solution according to the randomization result. Control group will receive a placebo saline solution containing autologous blood serum and treated group will receive a saline solution containing ABMMC. The solutions containing cells or placebo will be placed in opaque syringes (covered in 50% insulfilm), reinforcing the blind application, for injection.

In order to guarantee the quality of the material, imunophenotyping and clonogenic capacity analysis will be all done at a Core Lab as detailed in the appendix [see Additional file 1]. Cells will be kept in appropriate conditions and sent to the cells core lab for these analyses.

Exceeding material and cells collected from patients in the placebo group will be stored, duly frozen, until the end of the trial.

Bone marrow collected from patients included in control group will be used for phenotyping and cell analysis, which will be correlated with patients' clinical evolution.

